### Data analysis

Gait activity data monitored with the accelerometer is analyzed using a validated stroke-specific algorithm for gait detection and gait quantification in Matlab (The MathWorks Inc., Natick, MA, USA) [56]. This algorithm has shown to have good criterion validity and test-retest reliability in people after stroke. The algorithm detects gait activity with a minimum length of 8 s or a multiple of 8 s.

The effectiveness of the intervention on the primary outcome measure, USER-P Restrictions subscale, is assessed using random coefficient analysis. We include time of assessment, group assignment (intervention and comparison group) and the interaction between time of assessment and group assignment in the multi-level regression model. Because random coefficient analysis can handle missing data, the analysis is performed with all available data, including data from participants with incomplete datasets [57]. Intention-to-treat analysis will be applied. Also, for the secondary outcome measures (USER-P Frequency subscale, USER-P Satisfaction subscale, SIS-16, TUG, 6-MWT, FSS, HADS, FES-I, SS-QOL and gait activity) a comparable random coefficient analysis is performed to assess the effectiveness of the intervention. Demographic, injury-related and therapy-related variables of the 2 groups are examined using the independent *t* test or non-parametric equivalent, the Mann-Whitney *U* test. A *Χ*^2^ test is used to examine categorical variables. Furthermore, to compare the intensity of the training sessions in the VRT and non-VRT groups, the mean number of steps measured with the pedometer and the mean BORG-RPE score are analyzed with an independent *t* test or the non-parametric equivalent. Results are considered significant when *P* values are < 0.05.

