### Procedure

Participants in both the VRT and non-VRT group follow a training intervention of 2 30-min sessions per week for 6 weeks (12 sessions). Assessments are taken at baseline (T0), post intervention (T1, 6 weeks) and follow-up (T3, 3 months post intervention; Figs. 1 and 2). To promote participant retention, we plan training sessions in consultation with the participants and inform participants timely about the entire training schedule and the assessments. All outcomes are assessed in face-to-face meetings by the researcher ([name]). Data is collected on data collection forms, coded and entered into an electronic database by double data entry. The paper forms are stored in a locked cabinet and maintained for a period of 15 years. The researcher is responsible for the data management during the study. Adverse events (e.g., falls, pain and dizziness) that occur during the study period, whether or not related to the study intervention, are registered and in case of a serious adverse event the intervention will be discontinued for the participant. A serious adverse event is defined as an event that is fatal or life-threatening, requires hospital admission or extension of the admission, or causes invalidity or work disability. Participants in both groups continue to receive usual care and rehabilitation as provided by the rehabilitation center or other services in the area. The duration of gait-related therapies that participants visit parallel to the study intervention, are documented. Also, for each participant the adherence to the training sessions of the ViRTAS study is monitored by registering presence and any reasons for absence. In case the training intervention is discontinued for any reason, a participant is still requested to participate in the post intervention and follow-up assessments.

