### Outcome measures

During the baseline assessment several demographic, injury-related and therapy-related variables are identified. These variables are presented in Table 1.

**Table 1 Tab1:** Baseline demographic and clinical variables

Demographic variables	
Age of patient at inclusion	
Gender	
Height	
Weight	
Partner	
Living situation	
Region of residence	
Injury-related clinical variables	
Time since stroke at inclusion	
Type of stroke	
Site of stroke	
Use of walking aids	
Use of orthoses	
Medication	
Co-morbidities	
Functional Ambulation Category score	
Therapy-related variables	
Duration of gait-related therapies parallel to study intervention	

An overview of the measurement instruments used to assess the primary and secondary outcome variables is given in Table 2.

**Table 2 Tab2:** Outcome domains and measurement instruments

Outcome domain	Measurement instrument	Abbreviation	T0	T1	T2
Participation	Utrecht Scale for Evaluation of Rehabilitation-Participation	USER-P	X	X	X
Subjective physical functioning	Stroke Impact Scale-16	SIS-16	X	X	X
Fatigue	Fatigue Severity Scale	FSS	X	X	X
Anxiety and depression	Hospital Anxiety and Depression Scale	HADS	X	X	X
Falls efficacy	Falls Efficacy Scale International	FES-I	X	X	X
Quality of life	Stroke Specific Quality of Life Scale	SS-QOL	X	X	X
Walking ability	Six-minute walking test	6-MWT	X	X	X
Functional mobility	Timed-up & Go	TUG	X	X	X
Walking activity	Accelerometer monitoring (5 days)		X	X	X

T0: baseline, T1: post intervention (6 weeks), T2: follow-up (3 months post intervention)

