### Sample size

The sample size calculations are based on the primary outcome measure, the USER-P Restrictions subscale. A difference of 18.2 points on the USER-P Restrictions subscale is regarded as clinically relevant [32]. The standard deviation of the population is estimated at 17.9 points and the test-retest reliability (ICC) is suggested to be 0.85 [32]. Based on an alpha of 0.05 and a power of 80%, a minimum of 14 participants per group is necessary [55]. However, a relative high clinical relevant difference of 18.2 points (18%) is not expected in this study. Therefore, we re-estimated the sample size based on a difference of 15% (15 points) on the USER-P Restrictions subscale, resulting in a minimum of 21 participants per group [55]. Expecting a dropout rate of 20%, we assume that a minimum of 50 participants is needed to achieve a sufficient statistical power of 80%. The majority of the randomized studies regarding the effect of VR that are published up to now included less than 25 participants per group.

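### The primary model appears to estimate a free group difference at baseline; using the T0 score already collected would give a cheap, and at the protocol's own correlation small, gain in precision

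*Protocol article*

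**What the plan says.** The Data analysis section lists the terms of the primary model as "time of assessment, group assignment (intervention and comparison group) and the interaction between time of assessment and group assignment". It names no baseline covariate and does not constrain the group means to be equal at baseline. It adds that "the analysis is performed with all available data, including data from participants with incomplete datasets", and it plans a comparable model for each secondary outcome.

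The note to Table 2 (Outcome measures) gives the assessment times as "T0: baseline, T1: post intervention (6 weeks), T2: follow-up (3 months post intervention", and the Procedure section agrees on the first two: "Assessments are taken at baseline (T0), post intervention (T1, 6 weeks". Procedure labels the three-month assessment T3 and Table 2 labels it T2; I use T2. So the T0 score is collected for the primary outcome and for every secondary outcome in Table 2.

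The Sample size section supplies the planning values: "The standard deviation of the population is estimated at 17.9 points", a test-retest ICC of 0.85, a target difference of 15 points and 20% dropout. Under Randomization and blinding, allocation is 25 per group from one set of 50 envelopes, with no stratification described.

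**The concern.** If time of assessment includes T0, the group term in this model is the group difference at baseline. Randomisation makes that difference zero in expectation, yet the model spends information on estimating it. The time-by-group terms, which carry the treatment effect, then become differences in change from T0.

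Two things follow. First, the treatment estimate has a larger variance than a baseline-adjusted or baseline-constrained model would give from the same data. Second, when the groups differ by chance at T0, subtracting the whole difference over-corrects for it, because part of it would have regressed to the mean anyway. In a trial of 50 people without stratification on the baseline score, a chance difference of several points would be unremarkable. At stake is some precision, and a conditional shift in the estimate that can be avoided.

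**Working it through.** **Inputs from the protocol.** SD 17.9; ICC 0.85; target difference 15 points (18.2 in the first calculation); alpha 0.05; power 80%; 25 per group randomised, so 20 completers per group at 20% dropout. Sidedness is not stated; I take two-sided.

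**The plan's own figure.** A repeated-measures formula, n = 2 × [17.9 × (1.96 + 0.84)/difference]² × [1 + (T − 1) × ICC]/T with T = 3 and ICC 0.85, gives 15.18 × 0.9 = 13.67, so 14, at 18.2 points, and 22.35 × 0.9 = 20.12, so 21, at 15 points. Both match the stated numbers per group ("Based on an alpha of 0.05 and a power of 80%, a minimum of 14 participants per group is necessary"; then "re-estimated the sample size based on a difference of 15% (15 points) on the USER-P Restrictions subscale", giving 21). This is the variance of an average over visits, not of a time-by-group interaction, so the next step needs its own formulas.

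**Variance of the two analyses.** With rho the correlation between baseline and follow-up scores, categorical time and complete data:
- stated model (difference in change): 2 × SD² × (1 − rho) × 2/n
- baseline-adjusted or constrained model: SD² × (1 − rho²) × 2/n
- ratio, adjusted to stated: (1 − rho²)/[2(1 − rho)] = (1 + rho)/2, which is below 1 for every rho below 1.

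At rho 0.85 and 20 per group:
- stated SE = 17.9 × √(0.30 × 0.1) = 3.10; half-width 2.024 × 3.10 = 6.28
- adjusted SE = 17.9 × √(0.2775 × 0.1) = 2.98; half-width 2.024 × 2.98 = 6.04.

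**Conditional shift.** Given an observed baseline difference d, the stated model's estimate moves by −(1 − rho) × d. One standard error of d at 25 per group is 17.9 × √(2/25) = 5.06 points. Simulated slopes of the estimate on d were −0.15 at rho 0.85 and −0.51 at rho 0.50, as the formula predicts; the mean estimate was essentially zero, so there is no bias over repeated randomisations.

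**Results** (t-based, 20 per group, difference 15; stated vs adjusted):

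| rho | variance ratio | CI half-width | power | shift per 1 SE imbalance |
|---|---|---|---|---|
| 0.85 (protocol's ICC) | 0.925 | 6.3 vs 6.0 | 99.7% vs 99.8% | −0.76 |
| 0.70 (assumed) | 0.85 | 8.9 vs 8.2 | 91.5% vs 95.1% | −1.52 |
| 0.50 (assumed) | 0.75 | 11.5 vs 9.9 | 73% vs 85% | −2.53 |

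**Dropout.** Generalised least squares on the three-visit model with equal correlations, 25 per group and 5 per group leaving after T0, gives SEs at T1 of 3.08 vs 2.98 (rho 0.85), 4.32 vs 4.04 (0.70) and 5.52 vs 4.90 (0.50). The variance ratios become 1/1.065 = 0.94, 1/1.141 = 0.88 and 1/1.267 = 0.79. The gain shrinks a little because the free-baseline model uses the T0 scores of those who leave.

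**Where the stated model would miss 80%.** Change-score n per group is 22.35 × 2(1 − rho). It exceeds 21 when rho is below 1 − 21/44.71 = 0.53 (normal approximation).

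**The case against.** The strongest reply is that time, group and time-by-group is a common and valid longitudinal analysis, that nothing in the protocol is contradictory here, and that at the only correlation the protocol supplies the benefit is small. That stands, and it limits what may be concluded.

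A reader might infer that the trial is underpowered because of this model. The documents do not support that: at rho 0.85 power for 15 points is above 99% under either model. The loss is relative to a better model, not to the planned sample size. A reader might also infer that the estimate is biased. It is not; the shift exists only conditional on an observed imbalance, runs opposite to it, and at rho 0.85 is about 0.8 points per standard error, some 5% of the 15-point target (0.76/15).

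The correlations of 0.7 and 0.5 are mine. The ICC is a test-retest figure, whereas the relevant correlation spans 6 weeks to about 4.5 months in recovering patients. It may well be lower, but the protocol does not say by how much.

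The reading of the model is also partly inferred. The text does not state outright that T0 is a response, or whether time is categorical. With linear time the interaction is a slope difference, still with a free baseline group effect. If only T1 and T2 are outcomes, the text has no baseline adjustment at all, and an imbalance d carries through as rho × d (0.85 × 5.06 = 4.3 points), so using the baseline score is still the remedy.

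Finally, the equal-baseline constraint is not unconditionally safe. The text shown does not say whether T0 is completed before participants learn their allocation (the flowchart and schedule figures are not shown), and the primary outcome is self-reported.

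**Conclusion.** The point holds as a nearly free improvement. On the natural reading, the stated model estimates a baseline group difference that is zero in expectation and so gives up precision: 7.5% of the variance at rho 0.85 with complete data, about 6% with 20% dropout. At the protocol's own figure this does not endanger the planned power. It would matter materially only if the true baseline-to-follow-up correlation is well below the test-retest ICC; below about 0.53 the stated model would miss 80% power for 15 points. That is an assumption to be labelled as such, not something the protocol shows. The figures rest on T0 being in the outcome vector, categorical time, equal variances over time and a two-sided 5% level. This is not an error in the stated sample size or power.

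**What to change.** Keep the mixed model and its use of incomplete records. State that visit is categorical. Then choose one of two forms before the data are analysed:

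- If T0 is completed before allocation is disclosed, drop the group main effect and keep visit plus visit-by-group at T1 and T2, so that both arms share one baseline mean.
- Otherwise, or as an alternative, take T1 and T2 as outcomes with baseline USER-P Restrictions and its interaction with visit as covariates. This is close to the constrained model but not identical when data are missing, because participants with T0 only do not contribute. It does not assume equal baseline means, but it cannot repair a self-reported baseline that was influenced by knowing the allocation, so the timing of T0 should be stated in either case.

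Apply the same form to the secondary outcomes measured at T0. If only T1 and T2 were ever meant as outcomes, say so and use the covariate form.

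The cost is a line or two of model specification and one sentence on when T0 takes place. No new data are needed, and the article describes the trial as still ongoing.

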### Participants

Potential participants are included if they meet the following inclusion criteria: (1) diagnosed with stroke according to the World Health Organization (WHO) definition [27], (2) a time since stroke between 2 weeks and 6 months, (3) ability to walk without physical assistance for balance and coordination (i.e., patient may require verbal supervision or stand-by help from a person or may use a walking aid) (Functional Ambulation Category ≥ 3), (4) experiencing self-perceived constraints with walking in daily life, (5) living in the community and (6) age 18 to 80 years. Potential participants are excluded if they (1) have insufficient cognitive skills or understanding of the Dutch language to reliably answer simple questions (based on the impression of the researcher), (2) suffer from severe visual impairments, severe forms of ataxia or uncontrolled epileptic seizures or (3) currently suffer from orthopedic disorders or other co-morbidities that may limit walking ability. The last two criteria are verified with the participant and when needed checked in medical records.

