### Randomization and blinding

Participants are randomly assigned to the VRT group or the non-VRT group by an independent person who is not involved in the recruitment, intervention or assessments. The randomization is performed using sealed, opaque envelopes which contain a card stipulating to which group the participant is allocated. Twenty-five cards for both the VRT group and non-VRT group are placed in envelopes to ensure equal group sizes. The independent person picks a random envelope from the total set of envelopes and informs the participant and therapists about the treatment allocation. When randomization is done, the envelope is removed from the total set. The researcher who performs all assessments ([name]) is blinded to treatment allocation. Due to the nature of the intervention participants and physiotherapists providing the training intervention cannot be blinded to treatment allocation. Participants are explicitly asked not to disclose group allocation to the researcher. The assigned intervention is only revealed for the researcher when this is necessary to manage serious adverse events.

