
A foreseen difficulty of the study is that participants continue to receive usual care and rehabilitation which might interfere with the effect of the studied interventions. From an ethical perspective, it is not an option to withheld care or rehabilitation from subacute stroke survivors. As participants are within 6 months after stroke, they may receive other therapies focusing on gait. However, due to the randomization it is expected that there is no noticeable difference between the VRT and non-VRT group in the potential interference of usual care and rehabilitation. Still, the frequency and duration of the gait-related therapies are registered.

To the authors’ knowledge this is the first study to investigate the effect of a VR gait training intervention on the level of participation in people after stroke. VR gait training might be a great potential for rehabilitation after stroke.

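### The primary model leaves out time since stroke, which is recorded and ranges from 2 weeks to 6 months: valid on average, but open to avoidable chance shift and lost precision

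*Protocol article*

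**What the plan says.** All references are to the protocol article.

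- **Eligibility (Participants):** patients qualify with "a time since stroke between 2 weeks and 6 months".
- **Allocation (Randomization and blinding):** there are 25 cards per arm in one pool, and "The independent person picks a random envelope from the total set of envelopes". No stratification or minimisation is described. Participants and therapists are told the allocation.
- **Data collected (Outcome measures, Table 1):** time since stroke at inclusion is recorded. The same table, which is presented as baseline data, also contains "Duration of gait-related therapies parallel to study intervention".
- **Primary model (Data analysis):** a random coefficient model of USER-P Restrictions whose named terms are time of assessment, group and their interaction. No prognostic covariate is among them.
- **Baseline comparison (Data analysis):** "Demographic, injury-related and therapy-related variables of the 2 groups are examined using the independent" t test or Mann-Whitney U test, with a chi-square test for categorical variables and significance at P < 0.05. No use of the results is stated.
- **Co-intervention (Discussion):** on interference from usual care, "due to the randomization it is expected that there is no noticeable difference between the VRT and non-VRT group".

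**The concern.** The model terms are listed, so this is a choice the article has made and not a detail left to an analysis plan. The time-by-group contrast removes a chance difference between arms in the starting level of USER-P. It does not remove a difference in the rate of recovery. If someone who enters at 2 weeks tends to improve more over the following months than someone who enters at 26 weeks, an arm that happens to contain more early entrants will look better for that reason alone. With about 21 to 25 people per arm and no stratification, such a gap can be several weeks.

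The planned significance tests do not help. They leave the estimate as it is, and for true baseline variables any difference is due to chance by design.

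Parallel gait therapy is a separate matter. It accrues after allocation, so it is not a baseline variable, and randomisation does not guarantee its balance when participants and therapists know the arm.

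**Working it through.** **1. The plan's own figure.** Inputs from Sample size: SD 17.9, ICC 0.85, alpha 0.05 (two-sided assumed), power 80%, and differences of 18.2 and 15 points ("we re-estimated the sample size based on a difference of 15% (15 points) on the USER-P Restrictions subscale").

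- n per group = 2(1.96 + 0.84)² × SD²/difference², times the factor (1 + 0.85)/2 = 0.925 for two repeated measures.
- 15 points: 22.35 × 0.925 = 20.68, so 21, as stated.
- 18.2 points: 15.18 × 0.925 = 14.05, about the stated 14.

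The check below therefore uses 21 analysed per arm and 15 points as the yardstick.

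**2. Chance gap in time since stroke.** Assumption, not in the article: entry is uniform over 2 to 26 weeks.

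- SD = 24/√12 = 6.93 weeks.
- SE of the difference between arm means = 6.93 × √(2/21) = 2.14 weeks, so the 95% range is ±4.2 weeks.
- With 25 per arm the SE is 1.96 and the range ±3.8 weeks.

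**3. From weeks to USER-P points.** Assumption, not in the article: over the 24-week window, the latest entrants recover 5, 10 or 20 points less than the earliest. Slope = gradient/24, and 95% shift = slope × 4.19.

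| Gradient | Slope per week | 95% shift (points) | Share of 15 points |
|---|---|---|---|
| 5 | 0.208 | ±0.87 | 6% |
| 10 | 0.417 | ±1.75 | 12% |
| 20 | 0.833 | ±3.49 | 23% |

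**4. Precision and error rate.** The change from baseline stands in for the time-by-group contrast. Its residual SD is 17.9 × √(2 × 0.15) = 9.80, which takes the article's ICC as the correlation between assessments. In 40,000 simulated trials per setting, with 21 per arm and no treatment effect:

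| Gradient | SD of estimate, unadjusted | SD of estimate, adjusted | Type I error if gap > 3 weeks, unadjusted | Same, adjusted |
|---|---|---|---|---|
| 0 | 3.02 | 3.06 | 4.7% | 5.1% |
| 5 | 3.04 | 3.05 | 5.5% | 4.9% |
| 10 | 3.16 | 3.06 | 7.7% | 4.9% |
| 20 | 3.50 | 3.07 | 12.3% | 5.2% |

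- Over all trials, the unadjusted type I error is 4.9% to 5.1% and the estimate is unbiased.
- A gap above 3 weeks arises in about 16% of trials. In about 69% of those, the baseline t test on time since stroke is not significant.
- At the 20-point gradient, adjustment cuts the variance by 1 − (3.07/3.50)² = 23%. At zero gradient it raises the SD only from 3.02 to 3.06.

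**5. How the covariate must enter.** With T0 in the outcome vector, a main effect of time since stroke adds the same amount to each of a person's assessments and cancels in the change. In complete simulated data, adding it left the time-by-group estimates unchanged to four decimals. Only its interaction with time of assessment, or a model of the post-baseline values adjusted for baseline USER-P, does the work.

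**6. The baseline tests.** Table 1 has 7 demographic, 8 injury-related and 1 therapy-related variable. The therapy row is not a baseline variable, which leaves 15 true null comparisons. At 5% each, 15 × 0.05 = 0.75 false alarms are expected. The chance of at least one is 1 − 0.95¹⁵ = 54% if the tests are independent.

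**The case against.** The strongest reply is that nothing here is invalid. The standard error already reflects chance imbalance, every trial has unmodelled covariates, and an unstratified draw is a legitimate design. This stands. A reader might infer that the primary estimate is biased or its error rate inflated. Step 4 shows neither over randomisations, and the inflated rates apply only to trials that happen to be imbalanced.

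The second reply is that the article gives no link between time since stroke and change in participation. This also stands. The gradient is assumed, and at 5 points adjustment gains nothing in precision. A 2-week gap would move the estimate by only 0.4, 0.8 or 1.7 points (2 × slope) across the three gradients.

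The third reply concerns how the tests will be used. A reader might infer that significant baseline differences, or the parallel therapy variable, will decide which covariates enter the model. The article does not say so, and as written the baseline P values are a reporting weakness that cannot alter the primary result. Comparing co-intervention between arms is itself reasonable. The fault is its place among baseline variables and the reliance on randomisation to balance it.

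What remains is that the model is stated, the variable is already collected, and including it costs almost nothing even if the gradient is nil.

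**Conclusion.** The point holds as a worthwhile improvement, not as an error that undermines the trial. The listed model forgoes a recorded and plausibly prognostic variable. If recovery depends on time since stroke, the single trial's estimate carries a chance shift with a 95% range of about ±0.9 to ±3.5 points, or 6% to 23% of the 15-point design difference. The SD of the estimate is then 3.04 to 3.50, against 3.05 to 3.07 with adjustment. These figures rest on uniform entry over 2 to 26 weeks, 21 analysed per arm and gradients of 5 to 20 points, none of which except the 21 comes from the article. The precision gain also depends on the ICC of 0.85 serving as the correlation between assessments, and would be smaller with a lower correlation. The range of the shift in points does not depend on the ICC.

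Two smaller points need no assumption about the gradient. P values for true baseline variables answer no useful question. Parallel gait therapy is a post-randomisation measure placed in a baseline table.

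**What to change.** Before outcome data are examined:

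- **Primary model:** prespecify time since stroke at inclusion as a covariate, whatever any baseline test shows. If T0 stays in the outcome vector, include its interaction with time of assessment, and do not also enter baseline USER-P as a covariate. Alternatively, model only the post-intervention and 3-month values, with time since stroke and baseline USER-P as covariates.
- **Baseline table:** describe the 15 true baseline variables by arm and omit the P values.
- **Parallel gait therapy:** move it out of the baseline table, report it by arm as a post-randomisation process measure with a 95% confidence interval, and keep it out of the primary model. Reword the Discussion so that it does not rely on randomisation to balance this therapy.

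The cost is one or two degrees of freedom for the treatment contrasts and a small change to the analysis text. No further data are needed, and allocation is unaffected. According to Trial status, recruitment was still under way when the article appeared, so the change could be made before results are known.
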